# Effectiveness of a Person-Centered and Culturally Sensitive Course of Treatment in Arabic-, Turkish-, and Urdu-Speaking Individuals With Type 2 Diabetes (the ACCT2 Study): Protocol for a Pragmatic Randomized Controlled Trial

**DOI:** 10.2196/67319

**Published:** 2025-06-05

**Keywords:** immigrants, migrants, diabetes management, ethnic minorities, trial, well-being, public health, type 2 diabetes, culturally-sensitive, randomized controlled trial

## Abstract

**Background:**

Individuals with non-Western backgrounds consistently exhibit a higher risk of type 2 diabetes (T2D) than ethnic Danes. Factors such as health behaviors, limited health care access, and social determinants of health often contribute to this disparity. Culturally sensitive interventions are crucial; however, effective interventions for managing T2D in non-Western populations remain limited.

**Objective:**

This study aims to examine the effect of a 1-year person-centered and culturally sensitive intervention on improving glycemic control (hemoglobin A_1c_ [HbA_1c_]) in Arabic-, Turkish-, or Urdu-speaking individuals with T2D. The secondary objectives are to improve diabetes management and overall well-being.

**Methods:**

This study is designed as a 2-arm randomized controlled trial. A total of 96 women and men with T2D (HbA_1c_≥53 mmol/mol) speaking either Arabic, Turkish, or Urdu as their native language will be randomized for 1 year to a health care professional–assisted intervention group (person-centered and culturally sensitive course of treatment) or a control group (usual care) in a 1:1 ratio in Denmark. Assessments are scheduled at baseline and 1 year. The primary outcome is HbA_1c_, while lipids, blood pressure, and patient-reported outcomes, including well-being, diabetes management, health literacy, and use of and adherence to diabetes medication, are secondary outcomes. Feasibility and satisfaction are evaluated through interviews. The study is approved by the Ethics Committee of the Capital Region of Denmark (H-23042245).

**Results:**

A 5.0-mmol/mol change in HbA_1c_ is the minimally important difference, requiring 88 participants. To allow for uncertainties and dropouts, the total was increased to 96. As of January 2025, a total of 88 participants have been recruited. Recruitment was completed in March 2025. Data collection will continue until December 2025, with the first results expected by March 2026.

**Conclusions:**

This study will contribute to the limited knowledge regarding the effects of person-centered and culturally sensitive treatment approaches for T2D in Arabic-, Turkish-, or Urdu-speaking individuals. The study uses a robust methodological design and will present an alternative avenue for managing T2D and improving overall well-being. The study offers valuable insights into the experiences of participants and health care professionals, including potential obstacles and strategies for implementation in outpatient clinics.

**Trial Registration:**

ClinicalTrials.gov NCT06147245; https://clinicaltrials.gov/study/NCT06147245

**International Registered Report Identifier (IRRID):**

DERR1-10.2196/67319

## Introduction

European studies have steadily indicated that immigrant groups born in non-Western countries are at a significantly higher risk of developing type 2 diabetes (T2D) than the majority population [1-3]. In Denmark, immigrants from the Middle East exhibit a T2D incidence rate 2.5 times higher than native Danes [4,5] and face increased risks of complications [2,3,6]. Individuals with non-Danish ethnic backgrounds have poorer glycemic control [7,8], and a lower proportion receive diabetes monitoring and care within recommended intervals outlined in the Danish Diabetes guidelines [7].

Individuals with non-Western backgrounds experience difficulties in managing their diabetes effectively. This is due to factors such as health behavior, access to health care, and social determinants, as well as low health literacy, cultural norms, and language barriers that hinder access to and comprehension of information and treatment of diabetes [4,9-13]. Other factors include misconceptions about diabetes, inadequate adherence to medication regimens, lifestyle factors, limited social support, and lack of cultural competencies among health care professionals (HCPs) [1,13-16]. This emphasizes a need for culturally appropriate interventions to improve access to health care and support, but existing interventions often overlook these cultural considerations [17,18].

Resnicow et al [17] define cultural sensitivity as incorporating cultural characteristics, experiences, norms, values, behavioral patterns, beliefs, and environmental and social forces of a target population to design, deliver, and evaluate interventions. Despite some interventions tailored for cultural minority groups that have shown positive effects on hemoglobin A_1c_ (HbA_1c_) [19,20], recent research highlights a significant gap in person-centered and culturally sensitive interventions for individuals with T2D. Despite guidelines recommending a person-centered approach, there is a disconnect between theory and practice [21], and current diabetes self-management education and support programs often lack cultural competence and literacy-sensitive recommendations [22-24]. These findings underscore the need for more research on culturally sensitive, person-centered interventions to improve diabetes management and reduce health disparities, particularly in outpatient clinics [25-27]. This study aims to explore the effectiveness of a person-centered, culturally sensitive intervention for individuals with T2D speaking Urdu, Arabic, or Turkish to improve glycemic control, as well as diabetes management, health literacy, and overall well-being by using a pragmatic randomized controlled trial (RCT) design [28,29].

## Methods

### Objectives

The overall objective of this study is to examine the effect of a 1-year, person-centered and culturally sensitive intervention on alterations in glycemic control (HbA_1c_) in Arabic-, Turkish-, or Urdu-speaking individuals. Secondary objectives describe changes in cardiometabolic risk factors and patient-reported outcomes, including well-being, diabetes management, health literacy, and adherence to diabetes medication.

### Hypotheses

We hypothesize that a 1-year, person-centered and culturally sensitive intervention added to standard care will be superior for reducing HbA_1c_ in Arabic-, Turkish-, or Urdu-speaking individuals with T2D. Superiority will be claimed if the baseline-corrected difference between the 2 groups is equal to or surpasses the minimal important difference (5 mmol/mol) in favor of the intervention group and if the *P*<.05.

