### Statistical Considerations

#### Sample Size Calculation

A 5.0-mmol/mol change is the minimal difference for the primary outcome, HbA_1c_. This resulted in the total number of participants required to enter and complete this 2-arm, parallel-design trial of 88 participants. The sample size was estimated using a general linear model equivalent to a repeated measures mixed model with 2 time points (PROC GLMPOWER, SAS 9.4; SAS Institute). The estimation was based on the following conditions: an allocation ratio of 1:1, **α**=.05, **β**=.1, a mean HbA_1c_ level of 70 (SD 14) mmol/mol at each timepoint [44,45], and a correlation between repeated measures of 0.8 [46]. The total number of participants was multiplied by 1.1 to account for potential uncertainties in the conditions used in the power calculation and to account for potential dropouts, resulting in 96 participants.

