#### Statistical Analysis

An intention-to-treat analysis, encompassing all randomized participants, will be conducted upon completion of the last participant’s final visit. A per-protocol analysis will be carried out, including participants who demonstrate compliance throughout the intervention. Data will be presented using standard descriptive statistics, with means and SDs for normally distributed data and medians with IQRs for data not conforming to normal distribution. Changes from baseline and distinctions in delta values between groups will be assessed using linear mixed-effects models, considering the outcome as a function of group, time, and the interaction between group and time, and accounting for a participant-specific random intercept. The adequacy of assumptions regarding normality and homogeneity of variances will be verified through graphical methods, and data will be log-transformed for analysis and subsequently back-transformed for presentation. In cases where model assumptions are not met even after logarithmic transformation, nonparametric statistical tests will be used. Statistically significant findings will be determined with *P*<.05 (2-tailed). To assess the potential impact of missing data on the primary outcome, a sensitivity analysis will be conducted, involving multiple imputations with missing data at follow-up, which will be included in the imputation process with the control group. Results will be presented as estimated mean changes, accompanied by 95% CIs, degrees of freedom, and, if appropriate, the test value.

Covariables such as age, sex, diabetes duration, and so on, will be included in analyses to assess their potential influence on the outcomes. This approach will allow us to adjust for confounding factors and provide an accurate estimation of the intervention's impact. In addition, if the intervention proves effective, a health economic evaluation will be conducted to estimate the cost per person. This evaluation will consider direct costs, for example, staff time and technology, alongside potential cost savings from improved health outcomes, reduced complications, and fewer health care visits.

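### The superiority rule requires an estimate of at least 5 mmol/mol, the same difference the trial is sized on, so at that true difference the rule is met about half the time and the stated β=.1 does not describe it

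*Protocol article*

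**What the plan says.** The Hypotheses section makes the superiority claim depend on two conditions together. One concerns the size of the estimate: "Superiority will be claimed if the baseline-corrected difference between the 2 groups is equal to or surpasses the minimal important difference (5 mmol/mol". The other is a P value below .05, and the result must favor the intervention.

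The Sample Size Calculation starts from the same number: "A 5.0-mmol/mol change is the minimal difference for the primary outcome, HbA_1c". Its other inputs are "an allocation ratio of 1:1, α=.05, β=.1", an HbA1c mean of 70 ("SD 14) mmol/mol at each timepoint") and "a correlation between repeated measures of 0.8". The result is 88 completers, raised to 96 for uncertainty and dropout. The method named is a standard power routine for a general linear model with two time points, which gives the power of a significance test.

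The Statistical Analysis section sets the test level: "Statistically significant findings will be determined with *P*<.05 (2-tailed"). No section gives an expected effect larger than 5 mmol/mol, and none says that the condition on the size of the estimate entered the power calculation.

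**The concern.** The power figure and the success rule belong to different events. β=.1 is the chance of missing P<.05 when the true difference is 5. The trial's claim also needs the observed difference to reach 5. An unbiased, roughly symmetric estimate falls below its true value half the time. An intervention that delivers exactly the protocol's own minimal important difference would therefore miss the superiority claim about as often as it earned it. Many of those misses would be clearly significant results. A reader of the article would take the chance of a superiority claim at 5 mmol/mol to be 90%.

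**Working it through.** **Inputs (Sample Size Calculation; sidedness from Statistical Analysis).** Difference 5.0; SD 14 at each time point; correlation 0.8; two-sided α .05; β .1; 1:1 allocation; 88 completers, 96 enrolled.

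**Step 1: the plan's own figure.**
- SD of change = 14 × √(2 × (1 − 0.8)) = 8.85.
- Per arm for 90% power = 2 × (1.960 + 1.2816)² × 8.85² / 5² ≈ 65.9, so 66 per arm, total 132 (134 with the t distribution).
- With baseline adjustment (ANCOVA), the SD is 14 × √(1 − 0.8²) = 8.40 and the total is 120 (122 with t).
- The stated 88 is not reproduced. Power for P<.05 alone under the change-score model is 74.5% at 88 and 78.2% at 96 (78.8% and 82.3% with ANCOVA). This is a separate problem, and Steps 3 and 5 show that the 50% below does not depend on it.

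**Step 2: which condition binds.** SE = 8.85 × √(4/N). The smallest significant difference is the t critical value × SE.

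| Completers | SE | Smallest significant difference |
|---|---|---|
| 88 | 1.89 | 1.988 × 1.888 = 3.75 |
| 96 | 1.81 | 1.986 × 1.807 = 3.59 |

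With ANCOVA these differences are 3.56 and 3.40. All are below 5, so an estimate of 5 or more is in practice always significant, and the size condition decides. This holds while the SD of change stays below 5 / (1.988 × √(4/88)) = 11.8 at 88 completers, or 12.3 at 96.

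**Step 3: success at the planned effect.** P(estimate ≥ 5 | true 5) = P(Z ≥ 0) = 50%. Simulation of the joint rule (200,000 trials per sample size) gave 49.9% at 88 and 49.8% at 96.

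**Step 4: other true differences (change score).**

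| True difference | Rule met, 88 | Rule met, 96 | P<.05 alone, 96 |
|---|---|---|---|
| 4 | 29.8% | 29.0% | 59.1% |
| 5 | 50% | 50% | 78.2% |
| 6 | 70.2% | 71.0% | 90.8% |
| 7 | 85.5% | 86.6% | 96.9% |

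- True difference for 90% success: 5 + 1.2816 × 1.807 = 7.32 (96 completers); 5 + 1.2816 × 1.888 = 7.42 (88).
- Significant but not superior at a true difference of 5: 78.2% − 50% ≈ 28% (96 completers); 74.5% − 50% ≈ 25% (88).

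**Step 5: if the stated 90% at 88 were correct.** That would need an SE of about 1.53. Success under the rule at 5 would still be 50%. The significant-but-not-superior share would be 90% − 50% = 40%, and 90% success would need 5 + 1.2816 × 1.53 ≈ 7.0.

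**The case against.** The strongest defense is that the rule is a deliberate and conservative choice. A sponsor may decline to claim superiority for an estimate below its own minimal important difference. Adding the threshold only makes a claim harder: with no true effect, an estimate of 5 or more arises in about 0.3–0.4% of trials. The article calls 5 a minimal difference and nowhere presents it as the expected effect. It also commits to reporting estimated changes with 95% CIs and to publishing negative and inconclusive results, so a significant estimate of 4 would be visible. All of this stands, and it limits the harm to the superiority label and the power statement. It does not reconcile β=.1 at 5 mmol/mol with a rule that succeeds half the time there.

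Three stronger readings are tempting, and the document does not support them:

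- **That P<.05 can never matter.** This holds only near the planning variance. If the correlation were 0.6, the SD of change would be 14 × √0.8 = 12.5, the SE at 48 per arm 2.56 and the smallest significant difference about 5.08. The P condition would then bind, and success at 5 would fall below 50%.
- **That no sample size could help.** Once the smallest significant difference is below 5, this is true at a true difference of exactly 5. At 6 or 7, more participants raise the success rate, as the table shows.
- **That the rule causes the whole drop from 90% to 50%.** On the stated inputs the rule accounts for the drop from about 75–78% to 50%. The rest comes from the sample size not following from its inputs.

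One could also read the rule as requiring the confidence limit to clear 5. Success at a true difference of 5 would then be about 2.5%. The wording points to the estimate, so that reading is not used here.

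**Conclusion.** The mismatch is real: the stated β belongs to the significance test and not to the rule by which superiority will be claimed. At a true difference of 5 mmol/mol the rule is met about 50% of the time, at any sample size for which the smallest significant difference is below 5. That figure needs only an unbiased, symmetric estimate and an SD of change below about 12; the planning value is 8.85. The secondary figures depend on the inputs. A 90% success rate needs a true difference of about 7.3 to 7.4 mmol/mol on the planning inputs with 96 to 88 completers, or about 7.0 if the stated power were right. The share of significant results not called superior is about 28% at 96 completers. The rule itself is not invalid and does not inflate false claims. What is wrong is the power statement attached to it.

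**What to change.** **First choice.** Keep the published two-part rule and correct the power statement. State that β=.1 refers to P<.05 alone, and add that the full rule has about a 50% chance of success at a true difference of 5 mmol/mol and about 90% at 7.3–7.4 (SD 14, correlation 0.8, 96 to 88 completers). This costs one or two sentences and leaves the criterion unchanged. The power for P<.05 alone needs its own correction in the same place.

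**Alternative.** Through a dated amendment, documented before any outcome data by arm are examined, base the superiority claim on two-sided P<.05 in favor of the intervention. Report separately, as a statement of clinical relevance, where the estimate and its 95% CI lie relative to 5 mmol/mol. This has two costs. It relaxes a published criterion in an open-label trial whose recruitment is complete, raising the chance of a claim at a true difference of 5 from about 50% to about 78% (96 completers). A superiority claim would also no longer imply an estimate of at least 5, so the relevance statement would have to carry that message.

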### Participants

Women and men aged 75 years or younger with T2D whose native language is Urdu, Arabic, or Turkish will be considered eligible based on the specified inclusion and exclusion criteria.

### Eligibility Criteria

The inclusion and exclusion criteria are listed in Textbox 1. The eligibility criteria, including the age limit, were carefully selected based on several considerations. The language criteria were chosen to focus on the largest language groups at Steno Diabetes Center Copenhagen (SDCC), as individuals who speak fluent Danish generally face fewer challenges in managing their treatment and T2D compared with those with limited Danish proficiency. Regarding the age limit, participants older than 75 years were excluded as they are typically offered a different, combined approach to care. However, we recognize that older individuals need support, and it is believed that those younger than 75 years have the potential to become more self-sufficient with the right intervention. Therefore, the age limit was set to target those who could most benefit from this specific approach.

Inclusion and exclusion criteria.
**Inclusion criteria**
Men and women whose native language is Arabic, Turkish, or Urdu with limited to moderate proficiency in Danish.Already in treatment at the outpatient type 2 diabetes clinic at Steno Diabetes Center Copenhagen, Denmark.Having suboptimal glycemic control (hemoglobin A_1c_ [HbA_1c_] ≥53 mmol/mol).Individual treatment goal for HbA_1c_ has not been achieved (in 2 consecutive measurements).
**Exclusion criteria**
Being older than 75 years at inclusion.Residing part-time in Denmark.Having disabilities that inhibit physical attendance.Having severe mental disorders.Having an estimated glomerular filtration rate below 30 mL/min/1.73 m².General condition contraindicates continuing the study, judged by the investigator or medical expert.Withdrawal of the informed consent.Other reasons determined by the investigator.

### Recruitment, Screening, and Consent

We plan to recruit 96 Arabic-, Turkish-, or Urdu-speaking individuals with T2D from the outpatient T2D clinic at SDCC. During the latest visit to the usual course of treatment at SDCC, potential participants will receive a brief introduction to the person-centered and culturally sensitive course of treatment in the type 2 diabetes (ACCT2) study. If interested, potential participants will be met by a project worker who will provide an oral introduction and, if interested, play an audio recording containing study information in Urdu, Arabic, or Turkish, depending on the participant’s preference. All study participants will receive written study information in their native language. The information will be given in quiet surroundings at SDCC. The ability to bring one companion is allowed.

The project worker will have a written informed consent ready to sign and be available to address any questions. Participants may have at least 24 hours to consider participation. A participant folder containing the written study information and the written informed consent will be handed to the potential participant, and a project worker will follow up with a phone call within a week. If the participant wishes to take part in the study, the written informed consent must be signed and forwarded to the project worker. By January 16, 2025, a total of 88 out of 96 participants were recruited. The recruitment process will continue until March 2025.

To ensure accessibility, all written information is translated into Urdu, Arabic, or Turkish by international standards [30]. Study participants are informed that they can always withdraw their commitment to participate. The individual participant’s right not to know their data will be respected.

### Randomization

After obtaining written informed consent, participants will be randomized to either the intervention or control group in a 1:1 ratio using block randomization (Figure 1). Block randomization is used to secure an equal distribution of participants in the 2 groups if the study, for unexpected reasons, should be terminated before inclusion of all participants, and further to account for potential seasonal confounding.

**Figure 1 figure1:**

Randomization.

Randomization will be performed by the investigator before the first visit using the randomization module in the software REDCap (Research Electronic Data Capture; Vanderbilt University). The randomization list is created by a researcher not involved in the trial, who will be the sole person to access it throughout the trial. Should this person be unable to continue this function, a new person not involved in the trial will be appointed to store and access the sequence. Participants are recruited continuously.

### Patient and Public Involvement

The intervention was developed in collaboration with the target group and HCPs from the outpatient T2D clinic at SDCC. Overall, the ACCT2 study consists of three phases: (1) needs assessment, (2) intervention development and element testing, and (3) RCT.

Phase 1 (needs assessment) included interviews and workshops with Arabic-, Turkish-, or Urdu-speaking individuals with T2D (n=18) and 2 workshops and individual interviews with HCPs (nurses, physicians, and dieticians) from the SDCC outpatient clinic (n=33). The findings from the needs assessment suggested adjustments in the standard course of treatment by focusing on (1) extended time in consultations, (2) use of technology for diabetes monitoring, (3) awareness of language barriers, (4) meeting the same HCP, (5) use of accurate communication and dialogue tools, and (6) a need for increased levels of health literacy. A culturally sensitive approach of HCPs was also considered vital to increase understanding and engagement in diabetes management among the target group while emphasizing a whole-person approach rooted in individual everyday life.

Based on the results from the needs assessment (unpublished), a 1-year intervention was designed to target the target group’s needs. Visits in the intervention design were tested on 3 individuals speaking Urdu, Arabic, and Turkish as their native languages to test if the flow, content, and overall design match their needs. Tools and methods included in the intervention are partly inspired by the research-based diabetes self-management education, Culturally Sensitive Tools and Methods (CUSTOM) for individuals with non-Western backgrounds [31,32]. The RCT design is described in this study (phase 3). The CONSORT-EHEALTH (Consolidated Standards of Reporting Trials of Electronic and Mobile Health Applications and Online Telehealth) reporting guidelines were applied (Multimedia Appendix 1) [33].

